### Eligibility criteria {10}

Table 1 describes the eligibility and exclusion criteria for this trial. Participants must have physician documentation of GDM during any prior pregnancy. Given the diversity of clinically acceptable methods used to diagnose GDM [104–107], several diagnostic methods for prior GDM are eligible. Acceptable documentation to confirm prior GDM are as follows: (1) a 3-h 100 g oral glucose tolerance test (OGTT) performed at ≥ 20 weeks’ gestation in which 1 or more values exceeded the Carpenter and Coustan criteria [108] (i.e., fasting ≥ 95 mg/dL; 1 h ≥ 180 mg/dL; 2 h ≥ 155 mg/dL or 3 h ≥ 140 mg/dL), (2) a 75-g OGTT performed at ≥ 20 weeks’ gestation and 1 or more values exceeded the International Association of Diabetes and Pregnancy Study Groups (IADPSG) criteria [109] (i.e., fasting ≥ 92, 1 h ≥ 180; 2 h ≥ 153), (3) a 1-h 50 g test performed at any time during pregnancy with a value of ≥185 mg/dL (if ≥130 mg/dL but < 185 mg/dL and the clinic did not do a follow-up 100-g OGTT, the participant would be ineligible), (4) a fasting glucose value prior to 20 weeks’ gestation was ≥ 92 mg/dL and < 125 mg/dL and treatment with medication or insulin, or (5) an HbA1c conducted anytime during pregnancy with a value of > 5.6% and the treatment with medication or insulin.

**Table 1 Tab1:** Inclusion and exclusion criteria for Gestational Diabetes Prevention/Prevención de la Diabetes Gestacional

Inclusion criteria	Prior diagnosis of GDM
	Planning to have a baby in the next 1–3 years
	BMI > 25 kg/m^2^
	English- or Spanish-speaking
	Breastfeeding or non-breastfeeding
	Literacy ≥5th grade level
	Access to a cell phone
Exclusion criteria	Age < 18 years
	HbA1c test (> 6.5%)
	≥ 3 months postpartum
	Current pregnancy
	Tubal ligation Semi-permanent form of birth control with no plans for removal (e.g., hormonal progesterone intrauterine device or hormonal contraceptive implant)
	Relocating in the next 2 years
	Medications that affect weight or diabetes (e.g., oral corticosteroid and metformin)
	Use of weight loss medications
	Serious current physical disease (e.g., heart disease, cancer, renal disease, and diabetes) for which physician supervision of diet and exercise prescription is needed
	Orthopedic limitations to aerobic exercise
	History or plans of bariatric surgery
	Current problems with drug abuse and/or symptoms of an eating disorder, which occurred less than 3 years year ago

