#### Maternal/infant consequences of GDM

Chart abstractions are conducted by trained research staff to determine whether the intervention results in fewer adverse maternal and neonatal health outcomes. Consistent with prior research, rates of inadequate and excessive GWG are computed based on the National Academy of Medicine guidelines [118], using measured pre-pregnancy and last clinic visit weights. Other maternal adverse outcomes clinically defined based on chart abstractions include gestational hypertension, preeclampsia, cesarean delivery, labor induction, and delivery < 37.0 weeks’ gestation. Adverse outcomes among infants include birth weight greater than 4000 g, large size for gestational age (defined as birth weight above the 90th percentile), and small size for gestational age (birth weight below the 10th percentile) [144]. A composite measure of serious perinatal complications is defined as one or more of the following: death (stillbirth or neonatal death), hypoglycemia, hyperbilirubinemia, neonatal hyperinsulinemia, shoulder dystocia/birth trauma (brachial plexus palsy or clavicular, humeral, or skull fracture), admission to the neonatal intensive care unit (NICU), and respiratory distress syndrome [13, 145]. An additional composite morbidity outcome is computed based on prior research in women with obesity that includes at least one of the following: cesarean delivery, hypertensive disorders of pregnancy (HDP), birth weight ≥ 4000 g, birth weight < 2500 g, or NICU admission [146]. In women diagnosed with GDM, prescribed treatments are examined to explore whether the intervention impacted the intensity of treatment/severity of GDM.

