#### Demographics and medical/reproductive history

At baseline, participants complete a demographic questionnaire assessing age, race, ethnicity, and weight history (e.g., inter-pregnancy weight changes). Given prior relationships with GDM recurrence [148], extensive pregnancy history information (maternal and neonatal) are collected [149, 150]. At follow-ups, changes in smoking, prescription medications, unsafe dieting practices [117], job status, and participation in other weight loss programs, and changes in medical history are assessed. Pregnancy urine tests are used to assess pregnancy status at quarterly visits until conception. Pregnancy confirmation is documented through clinical ultrasound results.

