## Statistical methods

### Statistical methods for primary and secondary outcomes {20a}

A multiple logistic regression analysis will be used to examine the effect of the treatment group on the proportion of women who develop GDM. The model will include site and covariates to adjust for pre-randomization variables that may relate to the outcome, including parity, age, education, income, smoking, race/ethnicity, BMI, and time since last pregnancy. The effects of the pre-pregnancy weight loss intervention on weight, eating, activity, and physiologic outcomes will be examined using a linear mixed model with fixed effects for treatment condition (the between-groups factor), time (baseline, 16 weeks, 26 weeks’ gestation), site, and baseline covariates. Linear regression and logistic regression analyses will be performed to address the possible effects of the intervention on cases of excessive GWG, gestational hypertension, cesarean delivery, and large for gestational age at birth and 6 weeks, with site and baseline covariates entered in the models. A multiple linear regression analysis will also be used to examine the effect of the treatment group on composite scores of adverse maternal/neonatal outcomes, and logistic regressions will be used to examine separate effects on offspring obesity and odds of exceeding the National Academy of Science guidelines, including the same covariates described above.

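### Cesarean delivery is compared in women who have all been pregnant before, without naming prior cesarean as a covariate: a loss of precision in secondary endpoints, not a bias

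*Protocol article*

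**What the plan says.** Under Eligibility criteria {10}: "Participants must have physician documentation of GDM during any prior pregnancy". So every woman has had at least one earlier pregnancy.

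Under Maternal/infant consequences of GDM, the maternal outcomes taken from charts include "gestational hypertension, preeclampsia, cesarean delivery, labor induction, and delivery < 37.0 weeks’ gestation". The additional composite morbidity outcome is met by at least one of "cesarean delivery, hypertensive disorders of pregnancy (HDP), birth weight ≥ 4000 g, birth weight < 2500 g, or NICU admission". Neither definition separates first from repeat cesareans, or planned from unplanned ones. The other composite, of serious perinatal complications, does not contain cesarean.

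Under Statistical methods for primary and secondary outcomes {20a}, the primary model includes site and "covariates to adjust for pre-randomization variables that may relate to the outcome, including" the following: "parity, age, education, income, smoking, race/ethnicity, BMI, and time since last pregnancy". Regressions are then planned for "cases of excessive GWG, gestational hypertension, cesarean delivery, and large for gestational age at birth and 6 weeks, with site and baseline covariates entered". For the composites, the section chooses a linear model to "examine the effect of the treatment group on composite scores of adverse maternal/neonatal outcomes", and it carries the same covariates forward.

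Under Sequence generation {16a}, randomisation is stratified by site, pre-diabetes status and prior method of GDM diagnosis. Under Demographics and medical/reproductive history, "extensive pregnancy history information (maternal and neonatal) are collected" at baseline, the stated reason being the relation of that history to GDM recurrence. Prior mode of delivery is not named there.

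**The concern.** In women who have already delivered, the mode of an earlier delivery strongly influences the mode of the next. Many cesareans in the study pregnancy may be planned repeats, which a pre-pregnancy weight-loss programme has little chance to prevent. Parity does not stand in for this: two women of equal parity can have opposite delivery histories.

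The article sets its own test for a covariate, namely a pre-randomisation variable that may relate to the outcome. Prior cesarean plainly meets that test for cesarean delivery, yet the eight covariates named were chosen for the GDM model and are carried over to the obstetric outcomes.

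At stake is the sensitivity of the cesarean comparison, and to a lesser degree of the composite that contains it. A real reduction in first cesareans could go unseen among repeats.

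**Working it through.** **The plan's own figure.** The only power figure with full inputs is for GDM recurrence: 60% against 38%, 88 per arm, at least 81.98%. With two-sided alpha 0.05 (assumed, as none is stated) and mean proportion 0.49:
- null standard error = √(0.49 × 0.51 × 2/88) = 0.0754
- alternative standard error = √((0.60 × 0.40 + 0.38 × 0.62)/88) = 0.0735
- power = Φ((0.22 − 1.96 × 0.0754)/0.0735) = 83.7%

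An assumed design effect of 1.05 gives 81.9%. The figure reproduces. For prenatal and perinatal complications the article claims only more than 80% power for moderate effects and gives no cesarean rate, so no stated figure is disputed here.

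**Assumed inputs for cesarean.** Scenario A: 35% prior cesarean, control-arm cesarean risk 85% with and 15% without it. Scenario B: 45%, with 90% and 20%. Both use 88 per arm.

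**Share of control cesareans in women with a prior cesarean.**
- A: 0.35 × 0.85 / (0.35 × 0.85 + 0.65 × 0.15) = 0.2975/0.395 = 75%
- B: 0.45 × 0.90 / (0.45 × 0.90 + 0.55 × 0.20) = 0.405/0.515 = 79%

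Over a wider range (prior cesarean 20–50%, repeat cesarean 70–90%, first cesarean 15–25%) the share runs from 41% to 86%.

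**Power for cesarean.** Logistic regression with and without prior cesarean, 1000–2000 simulated trials per scenario. Ranges span A, B and repeated runs.

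| Conditional odds ratio | Acts in | Unadjusted | Adjusted |
|---|---|---|---|
| 0.4 | all women | 30–34% | 52–55% |
| 0.5 | all women | 18–24% | 33–37% |
| 0.4 | women without prior cesarean only | 11–13% | 18–24% |
| 0.5 | women without prior cesarean only | 9–10% | 12–14% |

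A second parametrisation uses the wider range above, with a risk ratio of 0.6 acting only in women without prior cesarean. It gives 6–21% crude, 7–29% stratified, and 14–32% when only women without prior cesarean are analysed. The overall risk ratio is then 0.76–0.94.

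**Why the unadjusted odds ratio differs.** Take scenario A with an odds ratio of 0.4 in both groups. Treated risks are 2.267/3.267 = 0.694 with prior cesarean and 0.0706/1.0706 = 0.066 without. The overall treated risk is 0.35 × 0.694 + 0.65 × 0.066 = 0.286. The marginal odds ratio is (0.286/0.714)/(0.395/0.605) = 0.61. Prior cesarean is perfectly balanced in this calculation, so the shift from 0.4 to 0.61 is non-collapsibility of the odds ratio.

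**Composite.** With 20–40% of women assumed to have another component independently, 80% repeat and 25% first cesarean, 26–65% of control events include a cesarean in a woman with a prior cesarean. Adjustment gains about 0–4 points when the effect acts only in women without prior cesarean. In scenarios A and B it gains up to about 6 points in the most favourable setting tried (effect in all women, odds ratio 0.4, other components 20%).

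**Type I error.** Simulated unadjusted tests of cesarean with no effect reject in about 4–6% of trials.

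**Chance imbalance.** The standard deviation of the arm difference in prior cesarean is √(2q(1 − q)/88), which is 0.060 at q = 20% and 0.075 at q = 50%. A difference of 10 points or more then has probability 10–18%.

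**The case against.** Several objections have force.

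- **The covariate list is not closed.** It is introduced by the word including, and an analysis plan that is not shown could add prior cesarean. This stands, and it limits the point to a recommendation. But the article does carry named covariates over to the obstetric outcomes, and a plan that followed those names would omit this one.
- **Randomisation balances prior cesarean in expectation.** This stands. A reader might infer that the unadjusted odds ratio is biased towards 1, or that the comparison is invalid. Neither follows: the marginal and conditional odds ratios are different quantities, and chance imbalance is already covered by the overall error rate. Adjustment still helps to interpret a trial in which an imbalance has occurred. Restricting the analysis to women who conceive weakens the protection of randomisation somewhat.
- **The large power gain needs an effect on repeat cesareans too.** This stands. If repeats are largely beyond the intervention's reach, the smaller gains apply and the endpoint stays underpowered even after adjustment.
- **Collection of prior delivery mode is inferred.** This stands; only pregnancy history in general is described.
- **Counting any cesarean is conventional.** It is, and it can stay; the point concerns the model, not the definition.

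A reader might also want previous macrosomia added to the birth-size models. The article's Risk factors section cites it as a risk factor for GDM, not for birth size, so the documents do not support that step.

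**Conclusion.** The point holds as a recommendation about precision in secondary endpoints. Prior cesarean is not a named covariate or a stratum, although every participant has been pregnant before and the article's own criterion for covariates would admit it.

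For cesarean alone, under the assumed rates, adjustment is worth roughly 20 points of power at an odds ratio of 0.4 if the intervention acts in all women, and roughly 7–13 points if it acts only in women without a prior cesarean. At 0.5 the latter gain is about 3–5 points. For the composite it is small.

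A reader might go further and infer that prior history drives both endpoints. The article gives no rate of prior, repeat or first cesarean, so that is not established: it is plausible for cesarean alone and not shown for the five-part composite. The simulated models held no other covariates, so the gain within the full planned model may differ. The primary outcome is unaffected.

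**What to change.** Before analysis, name prior cesarean (yes/no) as a covariate in the model for cesarean delivery and in the model for the composite that contains it. Take it from the baseline pregnancy history, or from chart abstraction if it was not recorded there. Report cesarean among women without a prior cesarean as a supportive analysis, with its limited power stated.

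The cost is one more term in models that already carry site and eight covariates for about 176 pregnancies, plus some abstraction work if delivery mode is missing from the baseline forms. Trial conduct, outcome definitions and the primary analysis do not change.

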### Objectives {7}

The Gestational Diabetes Prevention/Prevención de la Diabetes Gestacional is a two-site randomized clinical trial testing the efficacy of a pre-pregnancy lifestyle intervention to reduce GDM recurrence in women with overweight and obesity. The trial is following the CONSORT guidelines [103]. The primary hypothesis is that the recurrence of GDM will be reduced among participants assigned to pre-pregnancy lifestyle intervention vs. educational control group. Test for GDM will be conducted at 24 to 28 weeks’ gestation. Secondary hypotheses are that the pre-pregnancy lifestyle intervention (vs. educational control group) will result in improved maternal fasting glucose and biomarkers of insulin resistance (insulin, leptin, TNF-alpha, C-reactive protein, and adiponectin) and CVD risk (lipids and blood pressure) assessed before pregnancy, after 16 weeks of intervention, and at 26 weeks’ gestation. The pre-pregnancy lifestyle intervention (vs. educational control group) is expected to reduce adverse perinatal health outcomes for mothers (gestational hypertension, preeclampsia, preterm delivery, excessive gestational weight gain, induction of labor, cesarean delivery) and neonates (admission to the neonatal nursery, hyperbilirubinemia, birth trauma, weight for length *z*-scores ≥ 95% at birth and 6 weeks). Also, the pre-pregnancy lifestyle intervention (vs. educational control group) is hypothesized to result in greater pre-pregnancy weight loss and improvements in diet (calories, % fat, fast food) and physical activity (minutes of moderate activity). In exploratory mediator analyses, treatment-related changes in pre-pregnancy weight, eating, and activity are expected to be related to improvements in maternal physiology and reduced odds of GDM recurrence.

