### Outcomes {12}

#### Primary outcome

The study’s primary outcome is GDM diagnosis in the next pregnancy. The 2-step approach of diagnosing GDM is done at 24–28 weeks’ gestation and involves participants receiving as part of standard care a 50-g oral glucose solution followed by a 1-h venous glucose determination. Participants meeting or exceeding the 1-h screening criteria (a cutoff for an abnormal 1-h screen of ≥ 130 mg/dL) are then referred to the study for completion of the 100-g, 3-h diagnostic oral glucose tolerance test (OGTT). Positive diagnosis of GDM is based on the Carpenter and Coustan criteria [108] based on 2 abnormal values on the 3-h OGTT that includes a fasting value of > 95 mg/dL, 1 h > 180 mg/dL, 2 h > 155 mg/dL, 3 h > 140 mg/dL. The results of the study’s 100-g OGTT are immediately shared with the participants’ medical providers who interpret and inform patients of GDM screening results. If the study measured 100-g, 3-h diagnostic OGTT is not obtained, provider assessments done in standard care that are based on acceptable diagnostic methods (Table 2) are used to diagnose GDM. Final determination of GDM diagnosis is done by an independent evaluation of records from the study’s Ob/Gyn physician-researchers who are masked to the randomized group.

**Table 2 Tab2:** Diagnostic criteria for GDM in Gestational Diabetes Prevention/Prevención de la Diabetes Gestacional

1.	3-h 100 g OGTT performed at ≥ 20 weeks’ gestation in which 2 or more values exceed the criteria as follows: fasting ≥ 95 mg/dL; 1 h ≥ 180 mg/dL; 2 h ≥ 155 mg/dL or 3 h ≥ 140 mg/dL [108]
2.	75 g OGTT performed at ≥ 20 weeks’ gestation and 1 or more values exceed (fasting ≥ 92, 1 h ≥ 180; 2 h ≥ 153) [109]
3.	1-h 50 g test performed at any time during pregnancy with a value ≥ of 200 mg/dL
4.	Fasting glucose value prior to 20 weeks’ gestation ≥ 92 mg/dL and < 125 mg/dL and clinic treats the patient for GDM with medication or insulin
5.	HbA1c conducted anytime during pregnancy with a value ≥ of 5.7% and the clinic treats the patient for GDM with medication or insulin

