### Sample size {14}

Power calculations assume a 60% GDM recurrence rate in women with overweight or obesity [19, 57, 58]. With a target sample size of 252 participants and assumed ≥ 70% pregnancy rate [151, 152] and 30% lost to follow-up or not pregnant before conception, ≥ 176 pregnant participants (≥ 88 in each group) would provide adequate statistical power (≥ 81.98%) to detect intervention effects on the proportions developing recurrent GDM [83, 153], taking into account estimations of site-specific clustering effects and effect modifiers (i.e., weight status, ethnicity, parity) of GDM recurrence [24, 57]. Under this scenario, the minimum detectable effect size (odds ratio) would be 0.43, and proportions with GDM in educational control and intervention groups respectively would be 60% (*n* = 53/88) and 38% (*n* = 33/88). For secondary aims, 88 pregnancies in each group would yield > 80% power to detect effects equal to or smaller than those reported in prior work testing effects of lifestyle interventions on reductions in glucose, triglycerides, CRP [154], insulin, leptin [155], adiponectin [156], and blood pressure [157], taking into account estimations of site-specific clustering effects and effect modifiers (i.e., weight status, ethnicity, parity) of insulin resistance [158], and CVD risk factors [159, 160]. For secondary aims examining effects of the intervention on prenatal and perinatal complications, the study would have > 80% power to detect moderate effect sizes [161]. For the fourth aim examining the effects of the intervention on pre-pregnancy weight losses and improvements in eating (calories, macronutrient balance, fast food) and activity, 88 participants in each group would yield > 90% power to detect effects reported in prior work testing effects of lifestyle interventions on reductions in weight [157] and behavioral variables [162, 163]. For exploratory mediator analyses, > 80% power is achieved to detect > 21% increase in the mediated odds of GDM per kilogram difference in pre-pregnancy weight loss (equivalent to a mediated slope in a logistic model of > 0.189).

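### Treatment intensity is explored only among women who developed GDM, a subset the intervention is meant to change, so the comparison is open to selection of unpredictable direction

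*Protocol article*

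**What the plan says.** The outcomes section of the protocol article, under *Maternal/infant consequences of GDM*, fixes both the population and the question: "In women diagnosed with GDM, prescribed treatments are examined to explore whether the intervention impacted the intensity of treatment/severity of GDM". The population is women with GDM, and the question is causal.

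The event that defines this population is the trial's main endpoint (*Primary outcome*): "The study’s primary outcome is GDM diagnosis in the next pregnancy". The intervention is expected to change it (*Objectives {7}*): "The primary hypothesis is that the recurrence of GDM will be reduced among participants assigned to pre-pregnancy lifestyle intervention vs. educational control group". The sample size section puts figures on that expectation. The proportions with GDM in control and intervention "would be 60% (*n* = 53/88) and 38% (*n* = 33/88").

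The article gives no other denominator for treatment intensity, no severity scale with no GDM as its lowest level, and no caveat. The rule in section {20c} that all confirmed pregnancies are analysed is stated for the primary analysis.

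**The concern.** Randomisation makes the arms comparable. It does not make comparable the subsets that remain after the intervention has removed some women from one of them. If the trial succeeds as designed, about 20 women who would have had GDM under control are no longer in the intervention arm's GDM group. Any difference in treatment between the remaining 33 and the 53 control cases then mixes two things: an effect on severity in women who still develop GDM, and a change in which women those are.

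At stake is how a secondary finding is read. A higher drug-treated share among intervention cases could be reported as more severe disease when no woman was made worse. A lower share could be reported as milder disease without showing how much of it is selection.

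**Working it through.** **Inputs from the protocol article (*Sample size {14}*).** 88 pregnancies per arm; 53 control and 33 intervention cases. Check: 53/88 = 60.2% and 33/88 = 37.5%, which match the stated 60% and 38%. The stated odds ratio of 0.43 is slightly off these counts, since (33/55)/(53/35) = 0.40. With a 60% control rate it implies 39.2%, or about 34.5 cases. That does not change the argument below.

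**Assumed input.** The drug-treated share among control cases, s, is not in the article. The main illustration uses s = 40%; the range shown is 20% to 60%.

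**Condition for the direction.** Let m_C and m_I be the numbers of drug-treated women. The planned comparison sets m_C/53 against m_I/33. The share rises in the intervention arm only if m_I/m_C > 33/53 = 0.62, that is, if drug-treated cases fall by less than 38%. At s = 40%, m_C = 53 × 0.40 = 21.2 and the break-even is m_I = 13.2.

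**Four ways in which 53 cases could become 33, at s = 40%:**

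1. *Only diet-treated cases prevented.* m_I = 21.2. Within GDM: 21.2/33 = 64%. All pregnancies: 21.2/88 = 24% in both arms.
2. *Prevented cases drug-treated at half the average rate.* m_I = 21.2 − 20 × 0.20 = 17.2. Within GDM: 17.2/33 = 52%. All pregnancies: 17.2/88 = 20%, against 24%.
3. *Prevented cases a random sample of cases.* m_I = 21.2 − 20 × 0.40 = 13.2. Within GDM: 13.2/33 = 40%. All pregnancies: 13.2/88 = 15%, against 24%.
4. *Uniform downward shift of a normal latent severity.* The GDM threshold lies at −0.259 in control. To leave 37.5% above it, the shift must be 0.319 − (−0.259) = 0.578 SD. The drug-treatment threshold, with 24.1% above it in control, lies at 0.703. After the shift the upper tail beyond 0.703 + 0.578 = 1.281 is 10.0%. Within GDM: 0.100/0.375 = 27%. All pregnancies: 10%, against 24%.

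**Sensitivity to s (within-GDM share in the intervention arm):**

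| s in control | 1: diet-treated only | 2: half rate | 3: random | 4: uniform shift |
|---|---|---|---|---|
| 20% | 32% | 26% | 20% | 11% |
| 30% | 48% | 39% | 30% | 18% |
| 40% | 64% | 52% | 40% | 27% |
| 50% | 80% | 65% | 50% | 36% |
| 60% | 96% | 78% | 60% | 47% |

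The direction is set by the column, which is unknown, and not by s.

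**Could a spurious result look convincing?** In case 1 at s = 40%, rounded to whole women, 21/53 against 21/33 gives an odds ratio of (21/12)/(21/32) = 2.67 and a two-sided Fisher p of 0.045. For case 2, 21/53 against 17/33 gives p = 0.37. A nominally significant false signal therefore needs a rather extreme mechanism; a misleading point estimate does not.

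**The case against.** A reader might infer that the plan will make the intervention look harmful, and the more so the more GDM it prevents. The documents do not support that. Under the uniform shift (case 4) the prevented cases are also the mildest ones, yet the drug-treated share among the remaining cases falls from 40% to 27%, because the women who still have GDM are milder too. If prevented cases are a random sample, the share does not move. Prevention of mild cases is not enough to produce apparent worsening, and the article does not say which mechanism would apply.

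The item is also peripheral. It is worded as exploratory, appears neither among the hypotheses nor in the power statement, and has no model in section {20a}. An unseen analysis plan might handle it with care. That reduces the weight. It does not remove the point, because the article itself fixes the restricted population and the causal question.

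A further argument is that Table 2 builds drug treatment into some GDM definitions, for example "HbA1c conducted anytime during pregnancy with a value ≥ of 5.7% and the clinic treats the patient for GDM with medication or insulin". Such cases are drug-treated by definition, so the endpoint partly decides who enters the subset. But under *Primary outcome* these criteria apply only when the study's own 100-g OGTT is not obtained. They are fallback routes of unknown frequency, open to both arms, and nothing shows that they tilt the contrast. This is secondary.

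**Conclusion.** The point holds, with minor weight. The treatment-intensity comparison conditions on the primary outcome, so it is open to post-randomisation selection of unpredictable direction. With the protocol's 53 and 33 cases and an assumed 40% drug-treated among control cases, the intervention share could be anywhere from about 27% to about 64%, depending on which cases are prevented. The upper end arises with no woman made worse. The comparison can therefore show a spurious worsening, and alone it cannot say whether the intervention changed severity.

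The conclusion that selection is possible rests only on the article's own definitions and its expected effect. The sizes rest on the assumed drug-treated share and on simple prevention mechanisms. The primary analysis is unaffected.

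**What to change.** In the outcomes text under *Maternal/infant consequences of GDM*, define the between-arm comparison over all confirmed pregnancies. Use either drug-treated GDM (yes/no) or an ordered outcome: no GDM; GDM without drug treatment; GDM with medication or insulin. Compare by randomised arm. Keep the treatment table among women with GDM as description only, with no claim about the effect of the intervention.

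This puts the question on the same footing as the primary analysis, which uses the same set of pregnancies. At the assumed 40%, it gives 24% against 24% when only diet-treated cases are prevented, so no false harm appears. Under the uniform shift it gives 24% against 10%, so a real benefit shows.

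The cost is a sentence or two. Maternal outcomes are already abstracted from charts and GDM status is determined for the primary outcome, so no new data are needed. No clinical rule changes.
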